### Study Aim

Broadly, this study aims to evaluate the effectiveness of 3 contraceptive counseling approaches in improving modern contraceptive uptake in FHCs across Rawalpindi, Pakistan: sensitization, GATHER, and the BCS. Specifically, the study will determine the impact of each counseling intervention on modern contraceptive uptake, client satisfaction, and service provider competence at 3 and 6 months after the intervention; conduct a cross-sectional baseline analysis to examine sociodemographic, cultural, and health system factors associated with contraceptive use and discontinuation; identify key barriers and facilitators to contraceptive uptake through integrated quantitative and qualitative methods; compare uptake trends and determinants of contraceptive adoption between intervention and control groups; and generate context-specific evidence to inform the integration of scalable, rights-based counseling models into Pakistan’s national FP programs.

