### Study Design

This study is designed as a pilot, 3-arm, single-blinded, parallel, cluster-randomized pilot trial. It will evaluate the effectiveness of 3 counseling approaches (sensitization, as a control; GATHER; and the BCS) in improving modern contraceptive uptake. The trial will include both quantitative and qualitative components: a quantitative analysis to assess changes in contraceptive uptake, service provider competence, and client satisfaction; and a qualitative analysis to explore barriers, facilitators, and scalability. The unit of clustering is at the hospital catchment level, with FHCs nested within clusters considered as a single cluster and randomized to 1 of the 3 arms. The clustering at the hospital level is intended to minimize contamination across study arms. Clients enrolled in the trial will be blinded to the counseling strategy they receive.

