#### Service Providers: Universal Sampling

All service providers were enrolled in the trial through universal sampling. Eligible service providers had at least 6 months of experience in contraceptive counseling, were directly involved in FP service delivery, and were willing to participate through to completion of the study. For uniformity across the study arms, each arm enrolled 18 to 24 service providers for later training specific to their allotted arm. The total sample will thus be 36 to 48 service providers across both interventional arms, allowing adequate representation of service providers and assessment of the effect of training on the service providers’ competency and ability to promote contraceptive uptake.

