### Data Collection and Analysis

Data has been collected from structured facility records and client exit interviews at baseline (before the intervention) and will be collected 3 and 6 months after the intervention. Data quality will be ensured through descriptive statistics and logical validation checks, identifying missing values, inconsistencies, and outliers. The baseline characteristics will be summarized for assessing comparability across clusters.

The quality of FP services will be assessed using the Quick Investigation of Quality tool, which measure 25 key indicators of counseling quality [27]. For the data analysis, SPSS (version 26; IBM Corp) will be used. Service provider and client characteristics will be summarized in descriptive analyses. Exploratory comparisons will use paired 2-tailed *t* tests (or Wilcoxon signed-rank tests), ANOVA, and *χ*^2^ tests.

Mixed effects regression models with a random intercept for hospital catchment (cluster) will be using for clustering. These will be used to analyze binary outcomes of the interventions, such as uptake of modern contraceptives. Mixed effects logistic regression will be applied. For continuous outcomes, such as client satisfaction and quality score, we will use mixed effects linear regression. To assess robustness, population-averaged models using generalized estimating equations with robust SEs will be considered as a sensitivity analysis.

To estimate the changes in outcome over time between the interventional and control arms, we will use a difference-in-differences approach. All multivariate models will be adjusted for individual-level covariates such as age, parity, education, and baseline contraceptive use, as well as facility-level characteristics.

Effect sizes for categorical outcomes will be reported as odds ratios with 95% CIs, and for continuous outcomes, Cohen *d* will be used. Statistical significance will be assessed at a 2-sided *P* value <.05. Results will be presented in the form of tables and graphical summaries for interpretability and for informing future scalability.

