### Study Outcomes

The primary outcome will be uptake of modern contraceptive methods, and the secondary outcome will be client satisfaction and service provider competence. Follow-up assessments will be conducted 3 and 6 months after the intervention.

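### The stated model has no provider-level term: if service provider competence is analysed with it, the between-arm standard error of change is too large and power is lost

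*Protocol article*

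**What the plan says.** All statements are in the protocol article.

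- **Random structure.** Data Collection and Analysis: "Mixed effects regression models with a random intercept for hospital catchment (cluster) will be using for clustering". No provider effect, within-person covariance or hospital-by-round term is named anywhere.
- **Continuous outcomes.** Same section: "For continuous outcomes, such as client satisfaction and quality score, we will use mixed effects linear regression".
- **Change over time.** Same section: "To estimate the changes in outcome over time between the interventional and control arms, we will use a difference-in-differences approach".
- **Competence as an outcome.** Study Outcomes: "the secondary outcome will be client satisfaction and service provider competence". Study Aim places the assessments of "client satisfaction, and service provider competence at 3 and 6 months after the intervention". Study Design describes "a quantitative analysis to assess changes in contraceptive uptake, service provider competence, and client satisfaction".
- **Who is measured.** Service Providers: Universal Sampling says that eligible providers "were willing to participate through to completion of the study" and that "each arm enrolled 18 to 24 service providers for later training specific to their allotted arm". Results reports 48 providers recruited.
- **Other analyses.** Data Collection and Analysis also lists exploratory paired t or Wilcoxon signed-rank tests. Generalized estimating equations (GEE) with robust standard errors are to be considered as a sensitivity analysis, with no clustering unit stated.
- **Link to competence.** Quantitative and Qualitative Analysis and Integration includes competence among the outcomes to be analysed with allowance for the clustered design.

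**The concern.** Providers were enrolled once and asked to stay to the end, so their competence scores at successive rounds are repeated measures on the same people. A hospital intercept allows for similarity between people at one hospital. It does not allow for the greater similarity between two scores from one person. In a before-after contrast that similarity is what makes the estimate precise, and a model that ignores it reports an interval wider than the data justify. Competence is the outcome closest to the training being tested, so a real effect could be missed.

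For client outcomes the same single intercept makes a different assumption: that all hospitals in an arm move by the same amount between rounds. If they do not, that variation is left out of the standard error of the arm-by-round effect, and the error goes the other way.

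**Working it through.** The plan gives no standard error, sample size or power for competence, so there is no figure of its own to reproduce.

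**1. Provider competence**

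Inputs: two-sided 5% significance (Data Collection and Analysis); n = 24 providers per arm (the upper end of 18 to 24, assumed); one baseline and one follow-up score per provider (assumed); within-provider correlation r = 0.3, 0.5 or 0.7 (assumed, not in the document); hospital variance small. Scores are in SD units.

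- True variance of one provider's change: 2(1-r). True variance of the difference in mean change between two arms: 4(1-r)/n.
- Variance used with a hospital intercept only: about 4/n, because the hospital term cancels from the change and nothing represents the provider.
- Ratio of standard errors: 1/sqrt(1-r), whatever n is.

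| r | Ratio | True SE | Model SE | Effect with 80% power if provider is modelled | Power with hospital intercept only |
|---|---|---|---|---|---|
| 0.3 | 1.20 | 0.342 | 0.408 | 0.957 SD | 68% |
| 0.5 | 1.41 | 0.289 | 0.408 | 0.81 SD | 51% |
| 0.7 | 1.83 | 0.224 | 0.408 | 0.626 SD | 22% |

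At r = 0.5: true SE = sqrt(4 x 0.5/24) = 0.289 and model SE = sqrt(4/24) = 0.408. The test rejects when the estimate exceeds 1.96 x 0.408 = 0.800. With a true effect of 0.809, (0.809 - 0.800)/0.289 = 0.03, so power is about 51%. The false-positive rate is the two-sided tail beyond 1.96 x 1.414 = 2.77, about 0.6%.

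Two simulations agree, both assuming 3 hospitals per arm, 8 providers per hospital and ICC 0.02.

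- In 40,000 runs at r = 0.5, power was 52% with the hospital-only test and 78% with the provider-matched test. False positives were 0.8% and 5.0%.
- Fitted mixed models with three time points (about 105 to 111 usable runs per setting) gave standard error ratios of 1.14 at r = 0.3 and 1.42 at r = 0.5. Adding a provider intercept brought these to 0.98 and 1.02.

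**2. Client uptake**

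Inputs: ICC 0.02 and design effect 1.38 (Study Participants: Purposive Sampling and Sample Size Calculation). From 1.38 = 1 + (m - 1) x 0.02, m = 20, and 60 per arm / 20 = 3 hospitals per arm. The article does not state this number, so it is an assumption. Baseline clients per arm: 333/3 = 111, assuming an even split. Between-round hospital correlation c: assumed.

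- Variance in the model, per arm: 0.98 x (1/111 + 1/60) = 0.0252.
- Variance omitted, per arm: 2 x 0.02 x (1 - c)/3.

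| c | Omitted | True/model variance | False-positive rate |
|---|---|---|---|
| 0.8 | 0.0027 | 1.11 | 6.2% |
| 0.5 | 0.0067 | 1.26 | 8.1% |
| 0 | 0.0133 | 1.53 | 11.3% |

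Simulated binary data gave 6.2%, 7.9% and 11.0%.

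**The case against.** Competence is not explicitly assigned to this model. The continuous examples are client satisfaction and quality score, and the adjustment covariates (age, parity, education, baseline contraceptive use) are those of clients. No per-provider baseline competence score is described either: the data sources named are facility records and client exit interviews, and Results names only client satisfaction as preintervention outcome data. The article is condensed, and an analysis plan that is not shown could add a provider term. All of this stands, and it makes the point conditional. It does not remove it: the examples are introduced as illustrations, the integration section brings competence under the clustered analysis, and the only structure given for that stops at hospital.

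Two other provisions might seem to cover the gap. The paired tests recognise the pairing, but they are exploratory and describe change within a group, not the contrast between arms. GEE with robust standard errors clustered on hospital could in principle cover both problems, but it is only to be considered. In the smaller simulation with 6 hospitals it rejected a true null in 25% of runs at r = 0.3 and 18% at r = 0.5.

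A reader might infer more than the document supports:

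- *That competence scores are treated as fully independent.* They are independent given hospital.
- *That the trial will report false training effects on competence.* For change from baseline the error is conservative. If there were only the 3- and 6-month scores, the direction would be uncertain: pooling them as independent understates the standard error of their mean (ratio 1/sqrt(1+r), 0.82 at r = 0.5), but the estimated hospital intercept partly absorbs this.
- *That the uptake analysis is seriously invalid.* The excess is modest. With clients per arm held fixed it also shrinks as hospitals are added: 6 per arm at c = 0.5 gives about 6.5%, against 8.1% with 3.

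The power figures use 24 providers per arm, which the 48 recruited do not settle: 48 over three arms is 16 each, while 48 as the total for the two intervention arms leaves the control number unstated. The standard error ratio does not depend on this number.

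**Conclusion.** The point holds in conditional form. If competence is analysed with the stated model, as the article implies, and a baseline score was taken, the between-arm standard error of change is overstated by about 20%, 41% and 83% at within-provider correlations of 0.3, 0.5 and 0.7. With 24 providers per arm, 80% power becomes about 68%, 51% and 22%. The correlations, the provider number and the existence of a baseline score are assumptions. The direction is not in doubt for any materially positive within-provider correlation. This affects a secondary outcome in a pilot that was deliberately not sized for confirmatory power, so it is a worthwhile correction and not a threat to the primary result.

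For client outcomes the omitted hospital-by-round variation is a minor matter: about 6% to 8% false positives in place of 5% at between-round correlations of 0.8 to 0.5, and 11% only in the extreme case of no correlation.

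**What to change.** In Data Collection and Analysis:

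1. State the model for service provider competence: arm, round and arm-by-round, with a random intercept for provider nested in hospital. Alternatively, analyse the follow-up score adjusted for the same provider's baseline score, keeping the hospital term. Take the arm contrast from that model.
2. Say whether a baseline competence score was collected. Keep a pseudonymous provider code that links scores across rounds, since the article says that all data will be anonymized.
3. For client outcomes, add a sensitivity analysis that compares hospital-level changes between arms or includes a hospital-by-round random term.

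Items 1 and 2 need a change of wording and one linking code, with no extra participants or visits. Results states that no outcome data had been analysed at the date of this protocol version, so the change could still be prespecified from that position. The cost of item 3 is a somewhat wider interval for uptake, and with few hospitals the added term may be estimated at zero.

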#### Study Participants: Purposive Sampling and Sample Size Calculation

For the final phase of the trial, women of reproductive age visiting FHCs for FP services will be recruited through purposive sampling to compare client satisfaction and uptake of modern contraceptive methods before and after the intervention. The sample size estimate considered feasibility and the ability to inform future scale-up studies covering larger populations.

Baseline modern contraceptive uptake in all arms was assumed to be approximately 25% based on estimates from the Pakistan Demographic and Health Survey 2017‐18. A collective review of systematic reviews and meta-analyses revealed that improved counseling strategies can increase contraceptive uptake up to 30% to 40%, corresponding to an absolute increase of nearly 8% to 18% in comparison to routine care [23]. Based on the above evidence, we assumed values of 25% and 40% for contraceptive uptake in the control and interventional arms, respectively. An absolute effect size of 15% or 0.15 points was assumed for this study.

The sample size was calculated using a standard formula for comparing 2 populations through testing the 1-sided hypothesis. The significance level was set at 5% (α=.05) for a power of 80% (1−β=0.80). Given the design of the study, a pragmatic approach was used. Consistent with values reported in health services literature, an intracluster correlation coefficient (ICC) of 0.02 [25] and design effect of 1.38 (DE=1+(m-1) x ICC) was applied. Following methodological guidance for pilot trials, the sample size was not inflated to meet confirmatory power requirements, and a sample size of 60 per arm and 180 across all 3 arms was chosen.

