##### Randomization and Blinding

Cluster randomization was conducted at the hospital level, with each hospital constituting a cluster. Hospitals with similar characteristics were grouped to maintain comparability, and randomization was performed using computer-generated methods, with stratification to balance key variables such as hospital size and patient demographics. This strategy helps in minimizing contamination and bias in allocation.

For the interventional phase, the interventional arms are implementing the standardized counseling approach for which they were trained, whereas the control arm continues routine practices. Clients will remain blinded to the counseling approach they are provided, but owing to the nature of the interventions, the service providers know which arm they are assigned to. Although this is a study design limitation, it is standard practice in behavioral interventional trials.

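### With the roughly 3 hospitals per arm that the protocol's own figures imply, GEE with uncorrected robust SEs judged at P<.05 rejects a true null about 18% of the time, so it cannot serve as the robustness check; the main mixed model is only modestly liberal

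*Protocol article*

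**What the plan says.** - **Unit of randomisation.** Randomization and Blinding: "Cluster randomization was conducted at the hospital level, with each hospital constituting a cluster". Study Design gives the same unit, "with FHCs nested within clusters considered as a single cluster and randomized to 1 of the 3 arms". The nearly 60 family health centers (Study Setting) are therefore not the clusters.
- **Clustering figures.** The sample-size section for study participants assumes "an intracluster correlation coefficient (ICC) of 0.02" and says that a "design effect of 1.38 (DE=1+(m-1) x ICC) was applied". It settles on 60 clients per arm, 180 in all. Cluster size and number of hospitals are not given in the readable text, and the CONSORT figure is not shown.
- **Analysis.** Data Collection and Analysis makes mixed models with a hospital-level random intercept the main analysis. To assess robustness, "population-averaged models using generalized estimating equations with robust SEs will be considered as a sensitivity analysis". Multivariate models adjust for client covariates "as well as facility-level characteristics". Odds ratios carry 95% CIs, and significance is 2-sided P<.05.
- **Not mentioned.** The article names no degrees-of-freedom method, bias-corrected SE or cluster-level analysis.

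**The concern.** The sandwich variance estimates between-cluster variation from residuals around the arm means. With a handful of clusters per arm those residuals are systematically too small, and the estimate is itself noisy. Dividing by it and reading the ratio as standard normal makes both errors favour significance. The method named as the robustness check would then be less reliable than the model it is meant to check. A chance difference between a few hospitals could pass P<.05 in the main model and appear confirmed by GEE. The abstract expects the findings to guide national family planning programs, so misleading error bars matter even in a pilot.

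**Working it through.** **1. The protocol's figures and the number of clusters**

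- DE = 1 + (m − 1) × ICC, so m = (1.38 − 1)/0.02 + 1 = 20. Check: 1 + 19 × 0.02 = 1.38, which reproduces the stated value.
- Clusters per arm: 60/20 = 3. Total: 9. Between-cluster df after fitting three arms: 9 − 3 = 6.
- The 60 per arm is not the output of the stated formula. For 25% v 40%, 1-sided 5% and 80% power, the formula gives 120 per arm, or 120 × 1.38 = 166 with the design effect. The text presents 60 as a pragmatic pilot choice, so it is used here only to count clusters.

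**2. GEE with an uncorrected sandwich: a check by formula**

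Take k equal clusters per arm and two arms. The uncorrected variance is (k − 1)/k times the unbiased one, and the properly scaled ratio follows roughly t on 2(k − 1) df. The rejection rate under the null is therefore about P(|t| > 1.96 × √((k − 1)/k)) on 2(k − 1) df. For k = 3 this is P(|t₄| > 1.600) = 0.185.

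**3. The same by simulation**

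Inputs: null of 25% uptake in every arm, beta-binomial clusters of 20, ICC 0.02, normal reference. Rates are per pairwise comparison.

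| Hospitals per arm | Formula | Simulation |
|---|---|---|
| 2 | 30% | 30% |
| 3 | 18.5% | 17-18% |
| 4 | 14% | 13-14% |
| 6 | 10% | 10% |
| 10 | 8% | 8% |
| 20 | 6% | 6% |

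At 3 per arm, 95% CI coverage is 82.2% and the median SE is 74% of the true SD. The 17-18% hardly changes for ICC between 0 and 0.05. With one or two covariates that are constant within a hospital, rejection rises to 24% and 30%.

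**4. Mixed logistic model, normal reference, 3 hospitals of 20 per arm**

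Monte Carlo SE is about 0.6 to 1 percentage point.

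| ICC | No hospital-level covariate | One | Two |
|---|---|---|---|
| 0.02 | 7.1% | 8.7% | 9.1% |
| 0.05 | 9.5% | 11.8% | 14.2% |

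**5. Difference-in-differences**

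This uses a Gaussian approximation with a cluster random intercept only, ICC 0.02 and m = 20. The mixed model rejects 5% if hospital effects are stable over time, and 6-7% if their correlation over time is 0.8 to 0.5. GEE with robust SEs stays at 18-19%.

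**6. Alternatives at 3 hospitals of 20 per arm, ICC 0.02**

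- Cluster-level t test on 6 df: 5.1%.
- GEE with a Kauermann-Carroll-type SE and t on 4 df: 4.5%. The same SE with a normal reference still gives 11.6%, so the t critical value is needed as well.
- Mixed logistic model with t on 6 df: 2.4% (4.6% at ICC 0.05), so it is conservative at the protocol's ICC.

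**The case against.** - **The main analysis.** A reader might infer that the mixed model also has a false-positive rate well above 5%. At the protocol's ICC and implied cluster size it does not: about 7%, and near 5% for difference-in-differences with stable hospital effects. The 10-14% figures need ICC 0.05, which the protocol does not assume. This objection stands.
- **The cluster count is derived.** This stands. The section on stratified random sampling of centers also describes a lottery of centers, which blurs what a cluster of 20 would be. But the random intercept is fixed at the hospital catchment, and the GEE excess persists at 8% even with 10 hospitals per arm.
- **A normal reference is not written down, and an analysis plan not shown could add a correction.** This is fair, and it is why the percentages are conditional on an uncorrected test. However, the article does choose the method, calls it the robustness check and sets P<.05. Followed as written, it gives wrong intervals.
- **Facility covariates.** A reader might infer that every facility-level covariate costs one of the 6 df. Only covariates constant within a hospital do. With an assumed 4 centers per hospital, one or two center-level covariates leave the GEE rate at 18.4% and 19.2%, against 18.2% with none.
- **Multiplicity.** A reader might also count the unrestricted pairwise comparisons at two time points as part of the error. In a pilot described as exploratory, familywise control is a matter of preference, and the documents do not make its absence a mistake.
- **Pilot status.** The protocol waives confirmatory power. That does not excuse a nominal 95% interval that covers about 82%.

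**Conclusion.** The concern holds in limited form. For the GEE sensitivity analysis it is clear: about 18% rejection of a true null per comparison at the implied 3 hospitals per arm, and it cannot confirm or refute the main result. For the main mixed logistic model the excess is modest: about 7%, or about 9% with hospital-level covariates. These figures assume equal cluster sizes, beta-binomial clustering, covariates unrelated to outcome, a normal reference distribution and no small-sample correction. The number of hospitals is inferred from the protocol's own ICC, design effect and sample size; the size of the GEE problem varies with that number, from 30% at 2 per arm to 6% at 20. The point should be settled before outcomes are analysed, and the article reports that none have been.

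**What to change.** 1. State the number of hospitals randomised to each arm.
2. Base inference on between-cluster degrees of freedom (hospitals minus arms; 6 if there are 9 hospitals). Use either a cluster-level t/F analysis, or the mixed model with a named small-sample df method, noting that the latter can be conservative at ICC 0.02.
3. If GEE is kept, specify a bias-corrected sandwich (for example Kauermann-Carroll, Mancl-DeRouen or Fay-Graubard) together with t critical values. Confirm that the named software provides it; the cluster-level analysis needs only hospital means.
4. Limit covariates that are constant within a hospital to those used in the randomisation, and count their df. Two of them would leave 6 − 2 = 4 df and a critical value of 2.78. Client-level covariates can stay.
5. Optionally, test the overall three-arm effect before pairwise contrasts. This is a choice for a pilot, not a correction.

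**Cost.** Analysis wording only. Intervals widen: on 6 df the multiplier is 2.45 rather than 1.96, a factor of 2.45/1.96 = 1.25. Power of the cluster-level test for 25% v 40% with 3 hospitals of 20 per arm is about 24%, so results should be reported mainly as estimates with intervals.

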### Sampling Methods and Sample Size Calculation

#### Consecutive Sampling of Clients

In this initial phase, all eligible clients visiting selected tertiary care hospital–affiliated FHCs will be enrolled through nonprobability consecutive sampling. The sample size for this phase was calculated using the WHO sample size calculator [24], with a margin of error of 0.05, 95% CIs, and assumed prevalence of modern contraceptive uptake of 27%, as reported for Punjab in the Pakistan Demographic and Health Survey 2017‐18. A sample size of 333 participants was calculated using these parameters.

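### Baseline contraceptive use is adjusted for in every model, including the difference-in-differences model for uptake, where it is essentially the outcome's own baseline value

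*Protocol article*

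**What the plan says.** Under Data Collection and Analysis, binary outcomes such as uptake are to be analysed by mixed effects logistic regression. The only random effect named is an intercept for hospital catchment. Then: "To estimate the changes in outcome over time between the interventional and control arms, we will use a difference-in-differences approach". The following sentence reads: "All multivariate models will be adjusted for individual-level covariates such as age, parity, education, and baseline contraceptive use". Effects on categorical outcomes are reported as odds ratios. Under Study Outcomes: "The primary outcome will be uptake of modern contraceptive methods".

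On who is measured, the article points two ways.

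- Towards separate samples: "Data has been collected from structured facility records and client exit interviews at baseline", with the same sources planned at 3 and 6 months. For the consecutive first-phase sample, "A sample size of 333 participants was calculated using these parameters". For the final phase, where recruitment is purposive, "a sample size of 60 per arm and 180 across all 3 arms was chosen".
- Towards a cohort: Addressing Missing Data gives loss to follow-up as an example of a reason for missing values, and the covariate list treats baseline use as a property of the individual woman.

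**The concern.** Difference-in-differences already uses the baseline outcome: it forms the baseline rows of the data. Entering the same quantity as a covariate uses it twice. On the baseline rows of a cohort the covariate then predicts the outcome perfectly. A logistic model with one coefficient for baseline use must reconcile that with the weaker association at follow-up, and the arm-by-time term absorbs the mismatch. The word used for the scope of the adjustment is all, so the difference-in-differences model is not exempt. At stake is the size of the primary odds ratio, which readers would carry into the planning of the larger trial.

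If the women differ at each round, the problem is another one: the individual covariate has no measured value for anyone first seen at 3 or 6 months.

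**Working it through.** The protocol attaches no figure to this rule, so there is none to reproduce. The checks below show what the rule does. Hospital clustering is left out to isolate the point.

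**1. Cohort, size of the odds ratio.** Assumed: baseline uptake 25% in both arms; follow-up logit = −1.6 + 2.0 × baseline use + 0.7 × arm. The conditional odds ratio is exp(0.7) = 2.0. The implied follow-up uptake is 27.6% v 40.4%, close to the protocol's planning values of 25% and 40%. Large-sample fits:

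| Model | Log OR | OR |
|---|---|---|
| Difference-in-differences, no baseline use | 0.58 | 1.8 |
| Difference-in-differences plus baseline use | 1.09 | 3.0 |
| Follow-up uptake adjusted for baseline use | 0.70 | 2.0 |

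The 1.8 is the marginal odds ratio and the 2.0 the conditional one; both are legitimate targets. The 3.0 is neither. The pooled coefficient for baseline use is 3.9, against a true follow-up value of 2.0, because the baseline rows pull it up. With the arm effect set to 0, the interaction odds ratio is 1.0 with and without the covariate.

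**2. Cohort, dependence on the assumed correlation.** Baseline 25% in both arms and follow-up 25% v 40% give a true difference-in-differences odds ratio of (0.40/0.60)/(0.25/0.75) = 2.0. The latent correlation between a woman's two answers is not in the protocol and is varied:

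| Correlation | Without baseline use | With baseline use |
|---|---|---|
| 0 | 2.0 | 2.5 |
| 0.3 | 2.0 | 2.8 |
| 0.5 | 2.0 | 3.3 |
| 0.7 | 2.0 | 4.2 |
| 0.9 | 2.0 | 8.1 |

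The first row is the clearest. Baseline use carries no information about follow-up there, so conditional and marginal odds ratios are both 2.0, yet the planned combination gives 2.5.

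**3. Cohort, standard error.** Model of step 1 with no arm effect, logistic, 60 per arm, 1,500 runs, no term for the woman. Without baseline use, mean SE over empirical SD is 1.27 and the nominal 5% test rejects in about 1% of runs. With baseline use, the ratio is 0.90 to 0.93 over repeated runs and rejection is about 6% to 7%. In a linear model of the same kind the point estimate does not move when the covariate is added, but null rejection is 6.0% to 9.0% with it. Without it, rejection falls from 5.6% at correlation 0 to 0.7% at correlation 0.7. Woman-clustered standard errors without the covariate restore 4.5% to 5.2%.

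**4. Separate samples.** No arithmetic applies. A woman first interviewed at 3 or 6 months was not measured at study baseline. Prior use recalled at interview could be recorded, but that is a different variable and the article does not name it.

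**The case against.** The strongest case for the plan is that it is a condensed account of a declared pilot. The covariate list is illustrative, difference-in-differences is not named as the primary estimator, and a logistic model of follow-up uptake adjusted for a woman's own baseline use would be sound. Generalized estimating equations with robust standard errors are planned as a sensitivity analysis. The timeline and flow chart, which might settle the design, are not shown. Much of this stands, and it limits the point. It does not remove it: baseline use is named, the adjustment is said to apply to all multivariate models, and robust standard errors do not correct an odds ratio from a mis-specified mean model.

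Four stronger readings are tempting, and the document does not support them.

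- *Paired tests are planned on exit-interview clients.* The text says "Exploratory comparisons will use paired 2-tailed" *t* tests and assigns them to no unit. Service providers, who had to be willing to stay to completion and whose competence is an outcome, can be paired.
- *The clients are certainly repeated cross-sections.* The mention of loss to follow-up points the other way.
- *The standard error is 41% too wide.* With within-woman correlation 0.5, √(2/(2 × 0.5)) = 1.41, but this describes the model without the covariate. With it, the error is smaller and in the other direction.
- *Difference-in-differences costs 25% to 31% more variance than adjusting for cluster baseline uptake.* This assumes 9 clusters (design effect 1.38 with ICC 0.02 gives m = 20, and 180/20 = 9), cluster autocorrelation of 0.8 to 1, and a known slope. Estimating the slope from 9 clusters in 3 arms multiplies the adjusted variance by about 1 + 1/(6 − 2) = 1.25, so the ratio falls to 1.25/1.25 = 1.00 or 1.31/1.25 = 1.05.

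**Conclusion.** The point holds for the primary outcome. As written, the rule puts what is essentially the baseline outcome into a logistic difference-in-differences model for uptake. In a cohort this inflates a true effect on the odds ratio scale: 1.8 to 3.0 under one assumed model, and 2.0 to between 2.5 and 8.1 over assumed correlations of 0 to 0.9. It exaggerates a real effect; with balanced baselines it does not shift a null odds ratio away from 1.0. The standard error is somewhat too narrow with the covariate and too wide without it, because nothing accounts for a woman's repeated answers. With separate samples the individual covariate was not measured at study baseline for women first met at follow-up.

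The figures rest on assumed correlations and ignore hospital clustering. If baseline use also counts traditional methods, covariate and outcome coincide only nearly. For satisfaction and provider competence, contraceptive use is not the outcome's own baseline, so the double use does not arise there.

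**What to change.** 1. State whether clients are one cohort or a fresh sample at each round, and reconcile the sampling, data collection and missing-data sections with that.
2. Remove baseline contraceptive use from any difference-in-differences model for uptake.
3. If a cohort: either keep difference-in-differences with a woman-level random effect or woman-clustered standard errors, or analyse follow-up uptake adjusted for her own baseline use.
4. If separate samples: use difference-in-differences without individual baseline use, or follow-up uptake adjusted for the cluster's baseline uptake.
5. Choose one of these as primary in advance. They target different quantities when arms differ at baseline: with 25% v 35% at baseline and no change in either arm, difference-in-differences gives an odds ratio of about 1.0, while follow-up uptake adjusted for individual baseline use gives 1.4 to 1.5.
6. Limit paired tests to units measured twice, such as service providers.

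The cost is analysis wording and a little extra modelling. The Results section says no outcome data had been analysed at this protocol version, so the change could be made without knowledge of results.
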